## Abstract

**Background:**

Adolescent mothers have lower rates of initiation, continuation, and exclusivity of breastfeeding, and even more so in the first pregnancy. Current interventions target adult women, and little evidence is available for breastfeeding promotion among adolescents.

**Methods:**

This is a pilot study protocol with a parallel, single-blind, randomized, and controlled trial design, to evaluate the feasibility of the intervention “Lactation Counseling” in first-time adolescent mothers to maintain exclusive breastfeeding in the first 6 months of life. The control group will receive routine education in prenatal care and prenatal and childbirth classes, the experimental group will receive additionally the intervention “Lactation Counseling”, for 4 weeks, both conducted by trained nurses. Feasibility outcome includes recruitment and dropout rates, and, pilot outcomes will be the exclusive breastfeeding rate and the breastfeeding knowledge. Measurements will be taken at baseline, post-intervention, and 2, 4, and 6 months after childbirth.

**Discussion:**

Exclusive breastfeeding rates could be increased in adolescent mothers through nursing counseling interventions that are previously structured and evaluated from their feasibility. This study will allow the evaluation of the feasibility of an intervention in low-income, Latin American population adolescents.

**Trial registration:**

ClinicalTrials.gov NCT04655846, Registered 7 December 2020.

## Backgraund

Breast milk is the natural and optimal source of nutrition for the newborn; it is associated with multiple health benefits [1, 2], providing nutrients, hormonal immunoactives, and microbiomes necessary for growth and development [3]. Furthermore, in the mother, it reduces the probability of breast and ovarian cancers, improves birth spacing, prevents type 2 diabetes, obesity, and hypertension, among other benefits [4, 5].

Countries have made efforts to protect, promote and support exclusive breastfeeding (EB). It is expected that by 2025 the prevalence of EB will be 50% [6], although globally only about 38% of children benefit from it [7]. The outlook is worse in developing countries, such as Colombia with a prevalence of 36.1% in children under 6 months, and only 52.2% of children 6 to 12 months continued to receive breastfeeding [8].

Exclusive breastfeeding is one of the most important cost-effective strategies in the prevention of maternal and infant morbidity and mortality. An estimated 823,000 deaths of children under 5 years of age and 20,000 deaths of women from breast cancer could be prevented each year if breastfeeding were a universal practice [2].

The optimal practice of breastfeeding in adolescent mothers is determined by a range of personal and cultural factors such as attitudes about breastfeeding, perceived benefit, knowledge, previous experiences, self-efficacy, and affective or social support. All these factors significantly influence the duration of breastfeeding in adolescent mothers [9].

The development of educational strategies that intervene in the factors that influence breastfeeding in adolescent mothers is key. Therefore, nursing must acquire a commitment and responsibility in the implementation of educational interventions, motivating the mother to generate positive thoughts and attitudes, as well as providing a support network and knowledge that contribute to the significant improvement of breastfeeding practices and indices of initiation, exclusivity, and duration [10–14].

The Global Breastfeeding Scorecard 2019 urges that primary care facilities offer individual advice on infant and child feeding, seeking the goal of 80% of countries whose health institutions provide this advice by 2030. It emphasizes the importance of improving access to qualified breastfeeding counseling by providing specialized guidance that helps to make informed decisions and overcomes difficulties for breastfeeding, focusing on new mothers who have the greatest lack of knowledge and confidence [15].

To carry out educational interventions, the nurse must implement the nursing care plan, which provides patient-centered care and improves the expected results. To implement this care plan, the use of the Nursing Intervention Classification (NIC) [16] is recommended, which includes the nursing intervention “Lactation Counseling”; however, available evidence on the use of the classification in clinical trials is scarce especially in the adolescent maternal population [17].

## Purpose

This article describes the methodology of intervention design based on the nursing intervention “Lactation Counseling” that aims to determine the feasibility of this intervention in first-time adolescent mothers for maintaining exclusive breastfeeding in the first 6 months of child life.

As secondary objectives, we expect to estimate the recruitment and dropout rates, and the potential effectiveness of this intervention in the exclusive breastfeeding rate and breastfeeding knowledge.

## Methods

### Design

This is a pilot study protocol for a randomized controlled trial using a parallel-group design with a 1:1 allocation ratio, to evaluate the preliminary effect on exclusive breastfeeding rates of the intervention “Lactation Counseling” described in the Classification of Nursing Interventions (NIC) (16) (*n* = 59), versus usual education and nursing interventions not related to breastfeeding (*n* = 59) in first-time pregnant adolescents, attending the control prenatal, and followed-up with for up to 6 months after delivery (Fig. 1).

**Fig. 1 Fig1:**
[figure not shown]
Flowchart of the study protocol

### Participants

Eligible participants are first-time teenage mothers; between 14 and 19 years old, between 20 and 30 weeks gestation, and with the native Spanish language. Adolescents with psychiatric or communication disorders will be excluded and who have obtained a score greater than or equal to 3.8 on the Knowledge outcome: Breastfeeding (1800), described in the Nursing Outcomes Classification (NOC) [18].

### Settings and locations

The study will be carried out in two public hospitals in the cities of Girón and Piedecuesta in Santander, Colombia, which mainly provide care for low-income people. The recruitment of participants began in 2019 and is expected to end in 2021 due to delays caused by quarantines and restrictions to control the COVID-19 pandemic. The protocol is approved by the research ethics board of the Industrial University of Santander and is covered by the inter-institutional agreement between the participating hospitals; it has obtained approval and funding from the university’s Research and Extension Directorate (#2453) and additional funding from young research program form the Ministry of Science, Technology, and Innovation (#8009).

Pregnant women attending prenatal controls will be invited to participate in the study. Pregnant women who meet the inclusion criteria and sign informed consent will fill out a questionnaire designed based on the Knowledge outcome: Breastfeeding (1800). Adolescents who obtain a score on the knowledge test less than or equal to 3.8 points will be invited to participate in the intervention. Pregnant women scoring less than or equal to 3.8 in breastfeeding knowledge will be invited to participate as they are susceptible to increase breastfeeding knowledge.

### Interventions

#### Control group

This group will receive the usual education given in prenatal control and maternity preparation classes, using the interventions: Infant Care (6820) and Prenatal Care (6960), taken from the Nursing Interventions Classification [16]. This group will not receive specific interventions in breastfeeding and the information on this aspect will be that which is usually offered in prenatal control.

This group will receive the interventions in four educational sessions with the following topics: physical-psychological changes and care during pregnancy, the process of labor, delivery, and postpartum in its different stages, care of the newborn at home, and family planning. The sessions will be carried out in groups of a maximum of ten pregnant women, led by a nurse trained in maternal and perinatal care. The frequency of each session will be weekly, lasting between 45 and 60 min each. The sessions will be supported by audiovisual materials like slides, photography, videos, and educational games.

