#### Experimental group

In addition to the usual education given in prenatal control and maternity preparation classes, this group will receive the intervention “Lactation Counseling” (5244) defined as “assisting in the establishment and maintenance of successful breastfeeding” [16].

The intervention will consist of four educational sessions with seven topics (see Table 1). The frequency of each session will be weekly, lasting 45–60 min each. Each session contains three parts: (1) introduction to the topic where the objective of the session is explained and the pre-knowledge and usual practices in the community on the topic are explored, (2) development of the topic using PowerPoint presentations, audiovisual material such as photographs and videos, simulation material as well as strategies to encourage the participation of mothers such as games and challenges, and (3) end of the session reviewing the main lessons, addressing doubts and concerns, and carrying out an evaluation with questions on the topic of the session.

**Table 1 Tab1:** Summary description of educational sessions for Lactation Counseling intervention

Session	Content	Methodologies	Materials
1	• Composition of breast milk • Psychological and physiological benefits of breastfeeding	• Lecture method • Audiovisual Presentation • Group assignment	PowerPoint presentations Breast milk production video Breastfeeding benefits video Breastfeeding kit with educational elements such as games and models (bottles with types of breast milk) Explanatory sheets with each of the components of breast milk. Sheets with text to identify the benefits of the breast for the mother, baby, family, and society.
2	• Technique and positions for breastfeeding	• Audiovisual Presentation • Demonstration • Practical exercise	Simulated models (baby dolls) Video on breastfeeding and nipple latch technique
3	• Extraction, conservation, and administration of breast milk	• Lecture method • Audiovisual Presentation • Demonstration • Practical exercise	PowerPoint presentations Video on storage, conservation, and administration of breast milk. Vest-type simulators for breast milk extraction

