4	• Breast complications during breastfeeding • Lactating mother needs (rest, hydration, and a balanced diet)	• Lecture method • Audiovisual Presentation • Demonstration • Practical exercise • Group activity	PowerPoint presentations Breastfeeding kit with educational elements such as games and models (breast models) Lottery game on care and complications during breastfeeding Memory game on nutrition and hydration during breastfeeding Video on care for the prevention of breast complications

Participants will not receive educational material about interventions, neither will they be encouraged nor prohibited from seeking information about breastfeeding by other means. As a retention strategy, all mothers will be phone-called before each session to encourage their attendance and another phone call will be made during the first week after delivery to know the health status of the mother-child binomial.

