### Randomization and blinding

We will use simple randomization with an allocation ratio of 1:1. The generation of the allocation sequence will be carried out using a succession of true random numbers stored in tables of random digits. A person who does not know the participants will access this table to find out which group each participant belongs to, depending on whether the number was odd or even, and will inform the nurses who will carry out the intervention. The nurse who will perform the intervention “Lactation Counselling” will only maintain contact with the experimental group, and the nurse who will carry out the initial and final measurements along with the person who will perform the data analysis will be blinded to the group assignment. The nurses conducting the interview and statistical analysis of data will be masked in group assignments. To avoid contamination of the participants between the control group and the intervention group, they will meet on different days and times to attend the activities of the interventions.

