### Statistical analysis

The information will be recorded in EpiData 3.1. An intention-to-treat analysis will be performed. We will use descriptive statistics: continuous variables will be presented using median and standard deviation after evaluation of the normal distribution of the variable, otherwise, median and minimum, and maximum values will be used. The categorical variables will be presented in absolute frequencies and relative in percentages asymmetrical. Categorical data will be summarized as counts and percentages. The categorical and continuous variables will be compared according to the treatment group using chi-square tests or Fisher’s exact tests and Student's *t* test or Mann-Whitney's *U* test, respectively. The exclusive breastfeeding rate will be calculated at 2, 4, and 6 months of follow-up with their respective confidence intervals. To evaluate the preliminary effect of the intervention on the level of Knowledge: Breastfeeding, two approximations will be made by different statistical methods: mean differences through independent samples Student's *t* test and repeated measures ANOVA with their respective confidence intervals. Additionally, the effect of the intervention on the abandonment of exclusive breastfeeding will be calculated in terms of relative risk using binomial regression.

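### Mothers are randomised individually but taught in groups; the planned follow-up comparisons and the sample size make no allowance for correlation within a class

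*Protocol article*

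**What the plan says.** Under Randomization and blinding, the protocol article allocates individual mothers by simple 1:1 randomisation.

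Delivery is by group. Under Control group: "The sessions will be carried out in groups of a maximum of ten pregnant women", each class "led by a nurse trained in maternal and perinatal care", with four weekly sessions. Under Experimental group: "The intervention will consist of four educational sessions with seven topics", using "strategies to encourage the participation of mothers such as games and challenges". No group size is given there, but Table 1 lists a group assignment in session 1 and "Group activity" in session 4. These mothers receive the counselling "In addition to the usual education given in prenatal control and maternity preparation classes". To limit contamination between arms, "they will meet on different days and times to attend the activities of the interventions".

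Under Statistical analysis: "The categorical and continuous variables will be compared according to the treatment group using chi-square tests", or Fisher's exact, Student's t or Mann-Whitney tests. Knowledge is then analysed by an independent-samples t test and repeated measures ANOVA, and abandonment of exclusive breastfeeding by binomial regression for the relative risk. No term for class or nurse appears.

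Under Sample size for secondary outcomes there is no ICC or design effect. The one correlation used there (0.5) is between two assessments of the same mother.

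**The concern.** Mothers who attend the same class share sessions, discussion and group tasks, and the knowledge questionnaire measures what such sessions teach. Their outcomes may therefore be more alike than those of mothers from different classes. Because the arms meet separately, variation between classes feeds directly into the comparison of arms. A t test, chi-square test or ordinary binomial regression leaves that variation out of the standard error. Repeated measures ANOVA allows for correlation within a mother over time, not between classmates.

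At stake is the stated precision of the preliminary effect estimates, which the article promises with confidence intervals and a relative risk. In addition, if class membership is not recorded, it may not be possible to estimate the within-class correlation afterwards, and that quantity would help in planning a larger trial.

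**Working it through.** **Inputs from the article.** Exclusive breastfeeding 70% against 40%, power 80%, alpha 5% (two-sided assumed; the article does not say). Knowledge difference 0.4, SD 0.5, power 95%. Losses 20%; 59 mothers per arm. Control class size at most ten.

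**Assumed inputs.** ICC 0.01 to 0.05, since the article gives none. Class size *m* of five or ten participants in both arms.

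**The plan's own figure.** The two-proportion formula with d = 0.30 and mean proportion 0.55 gives

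n = [1.96·√(2·0.55·0.45) + 0.842·√(0.7·0.3 + 0.4·0.6)]² / 0.30² ≈ 42 per arm.

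The continuity correction raises this to 49. Then 49 × 1.2 = 58.8, so 59 per arm and 118 in total. The stated size is reproduced exactly under independence. Knowledge needs only 41 per arm before losses, so breastfeeding sets the number.

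**Effect of clustering.** Design effect DE = 1 + (m − 1)·ICC. The standard error grows by √DE, the true two-sided alpha is 2·[1 − Φ(1.96/√DE)], and the effective number per arm is n/DE.

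| m | ICC | DE | SE × | True alpha |
|---|---|---|---|---|
| 5 | 0.01 | 1.04 | 1.02 | 5.5% |
| 5 | 0.05 | 1.20 | 1.10 | 7.4% |
| 10 | 0.01 | 1.09 | 1.04 | about 6% |
| 10 | 0.02 | 1.18 | 1.09 | 7.1% |
| 10 | 0.05 | 1.45 | 1.20 | 10.4% |

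**Breastfeeding power.** After 20% loss, 59 × 0.8 ≈ 47 completers per arm. Power = Φ{[0.30·√n − 1.96·√0.495] / √0.45}, without continuity correction, with n the effective number:

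- independence: n = 47, power 84%;
- m = 10, ICC 0.01: 47/1.09 = 43.1, power 81%;
- m = 10, ICC 0.05: 47/1.45 = 32.4, power 69%;
- m = 8 (losses spread evenly over classes of ten): 82% at ICC 0.01 and 72% at ICC 0.05.

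**Knowledge power.** Power = Φ[(0.4/0.5)·√(n/2) − 1.96]:

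- independence: n = 47, power 97%;
- m = 8, ICC 0.05: 47/1.35 = 34.8, power 92%;
- m = 10, ICC 0.05: n = 32.4, power 90%.

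These powers are for an analysis that allows for class, before any further loss from having few degrees of freedom. At ICC = 0 nothing changes.

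**The case against.** The strongest reply is that the problem may be small here.

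- **Ten is a ceiling, and for one arm.** The article caps control classes at ten women, does not say that all are trial participants, and gives no size for the experimental arm. Recruitment ran from 2019 to an expected end in 2021 at two hospitals. Suppose even accrual over 13 to 36 months and separate classes per hospital and arm (four streams). Then 118/4/36 ≈ 0.8 to 118/4/13 ≈ 2.3 mothers join each stream per month, or about 2 to 5 over the ten-week gestation window. With three per class, DE is 1.02 to 1.10 and true alpha 5.2% to 6.2%. This stands as a reason to show the smaller class sizes.
- **A shared nurse need not add correlation.** Randomization and blinding refers to a single counselling nurse. If one nurse teaches every experimental class, her effect does not vary between those classes; it is confounded with arm, and a class term cannot remove it. The Discussion also asks for standardised, supervised delivery, which should reduce variation between classes. Both points stand, but shared discussion and group tasks remain.
- **Timing and status of the outcomes.** Breastfeeding is assessed at home 2 to 6 months after birth, well after the classes, and effectiveness is secondary to feasibility. This limits the consequence without removing it.
- **Detail left to a fuller document.** Data fields may well be. But the article itself names the tests and fixes 118 with 80% and 95% power, and those stated choices do not match the stated delivery.

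A reader might infer that both arms are taught in closed classes of ten, or that every planned test is invalid. The article does not support either. It never says that membership is fixed, and changing membership could weaken the clustering. Baseline knowledge is measured before classes start, so baseline comparisons of individually randomised mothers are sound.

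**Conclusion.** The point holds conditionally. Group teaching nested within arm is documented, and the named follow-up analyses and the sample size assume independence. Whenever the within-class ICC is positive, the intervals for the preliminary effects on knowledge and exclusive breastfeeding are too narrow.

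The size rests on an assumed ICC and class size. It is slight at ICC 0.01 or in small classes, and material at ICC 0.05 in full classes of ten, where true alpha is about 10% and breastfeeding power about 69%. It would be tempting to call the trial underpowered. The figures do not support that in general: breastfeeding power stays above 80% at ICC 0.01, and knowledge power stays at about 90% or more throughout the range shown.

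The primary feasibility outcomes do not depend on these comparisons. This is a correction that should be made; it does not threaten the pilot's main purpose.

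**What to change.** - Record a class identifier for every mother in both arms. Where experimental mothers attend usual classes as well as counselling sessions, record both; the article does not say whether these are the same groups.
- Add a random intercept for class, with small-sample degrees of freedom, to the follow-up knowledge model.
- For the relative risk of abandoning exclusive breastfeeding, use standard errors clustered on class with a small-sample correction.
- Report the ICC with its interval and say that it is imprecise. With 12 classes of about eight and a true ICC of 0.05, its standard error is about 0.07, so the interval runs from roughly 0 to 0.05 + 1.96 × 0.07 ≈ 0.19. It should not be the sole basis for sizing a later trial.
- State in the sample-size section that the 80% and 95% power figures assume no clustering by class.

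The cost is one data field (two where groups differ), some analysis wording, somewhat wider intervals, and few degrees of freedom: about ten for the comparison of arms if there are about a dozen classes. No extra participants are needed.

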#### Experimental group

In addition to the usual education given in prenatal control and maternity preparation classes, this group will receive the intervention “Lactation Counseling” (5244) defined as “assisting in the establishment and maintenance of successful breastfeeding” [16].

The intervention will consist of four educational sessions with seven topics (see Table 1). The frequency of each session will be weekly, lasting 45–60 min each. Each session contains three parts: (1) introduction to the topic where the objective of the session is explained and the pre-knowledge and usual practices in the community on the topic are explored, (2) development of the topic using PowerPoint presentations, audiovisual material such as photographs and videos, simulation material as well as strategies to encourage the participation of mothers such as games and challenges, and (3) end of the session reviewing the main lessons, addressing doubts and concerns, and carrying out an evaluation with questions on the topic of the session.

**Table 1 Tab1:** Summary description of educational sessions for Lactation Counseling intervention

Session	Content	Methodologies	Materials
1	• Composition of breast milk • Psychological and physiological benefits of breastfeeding	• Lecture method • Audiovisual Presentation • Group assignment	PowerPoint presentations Breast milk production video Breastfeeding benefits video Breastfeeding kit with educational elements such as games and models (bottles with types of breast milk) Explanatory sheets with each of the components of breast milk. Sheets with text to identify the benefits of the breast for the mother, baby, family, and society.
2	• Technique and positions for breastfeeding	• Audiovisual Presentation • Demonstration • Practical exercise	Simulated models (baby dolls) Video on breastfeeding and nipple latch technique
3	• Extraction, conservation, and administration of breast milk	• Lecture method • Audiovisual Presentation • Demonstration • Practical exercise	PowerPoint presentations Video on storage, conservation, and administration of breast milk. Vest-type simulators for breast milk extraction
4	• Breast complications during breastfeeding • Lactating mother needs (rest, hydration, and a balanced diet)	• Lecture method • Audiovisual Presentation • Demonstration • Practical exercise • Group activity	PowerPoint presentations Breastfeeding kit with educational elements such as games and models (breast models) Lottery game on care and complications during breastfeeding Memory game on nutrition and hydration during breastfeeding Video on care for the prevention of breast complications

Participants will not receive educational material about interventions, neither will they be encouraged nor prohibited from seeking information about breastfeeding by other means. As a retention strategy, all mothers will be phone-called before each session to encourage their attendance and another phone call will be made during the first week after delivery to know the health status of the mother-child binomial.

